**LIST OF ABBREVIATIONS AND RELEVANT DEFINITIONS**

|                |                                                                                                                                                                                                                                                                                                                                                  |
|----------------|--------------------------------------------------------------------------------------------------------------------------------------------------------------------------------------------------------------------------------------------------------------------------------------------------------------------------------------------------|
| ABR     | ABR form (General Assessment and Registration form) is the application form that is required for submission to the accredited Ethics Committee (ABR = Algemene Beoordeling en Registratie)                                                                                                                                                |
| AE      | Adverse Event                                                                                                                                                                                                                                                                                                                             |
| AR      | Adverse Reaction                                                                                                                                                                                                                                                                                                                          |
| CA      | Competent Authority                                                                                                                                                                                                                                                                                                                       |
| CCMO    | Central Committee on Research Involving Human Subjects                                                                                                                                                                                                                                                                                    |
| CV      | Curriculum Vitae                                                                                                                                                                                                                                                                                                                          |
| DSMB    | Data Safety Monitoring Board                                                                                                                                                                                                                                                                                                              |
| EU      | European Union                                                                                                                                                                                                                                                                                                                            |
| EudraCT | European drug regulatory affairs Clinical Trials GCP Good Clinical Practice                                                                                                                                                                                                                                                               |
| IB      | Investigator's Brochure                                                                                                                                                                                                                                                                                                                   |
| IC      | Informed Consent                                                                                                                                                                                                                                                                                                                          |
| IMP     | Investigational Medicinal Product                                                                                                                                                                                                                                                                                                         |
| IMPD    | Investigational Medicinal Product Dossier                                                                                                                                                                                                                                                                                                 |
| METC    | Medical research ethics committee (MREC); in Dutch: medisch ethische toetsing commissie (METC)                                                                                                                                                                                                                                            |
| (S)AE   | Serious Adverse Event                                                                                                                                                                                                                                                                                                                     |
| SPC     | Summary of Product Characteristics (in Dutch: officiële productinformatie IB1-tekst)                                                                                                                                                                                                                                                      |
| Sponsor | The sponsor is the party that commissions the organisation or performance of the research, for example a pharmaceutical company, academic hospital, scientific organisation or investigator. A party that provides funding for a study but does not commission it is not regarded as the sponsor, but referred to as a subsidising party. |
| SUSAR   | Suspected Unexpected Serious Adverse Reaction                                                                                                                                                                                                                                                                                             |
| Wbp     | Personal Data Protection Act (in Dutch: Wet Bescherming Persoonsgegevens)                                                                                                                                                                                                                                                                 |
| WMO     | Medical Research Involving Human Subjects Act (Wet Medisch-wetenschappelijk Onderzoek met Mensen)                                                                                                                                                                                                                                         |

## SUMMARY

**Rationale:** X-linked adrenoleukodystrophy (X-ALD) is a peroxisomal disorder, characterized by accumulation of very long-chain fatty acids (VLCFA; >C22:0) with highly variable expression. For a large category of patients there is no curative treatment. Experiments with bezafibrate in primary fibroblasts from patients with X-ALD and X-ALD knockout mice suggest bezafibrate can reduce VLCFA accumulation in X-ALD, the biochemical hallmark of the disease. This warrants further study to see if these findings can be reproduced in patients with X-ALD.

**Objective:** To determine if bezafibrate can reduce VLCFA in plasma, leukocytes and erythrocytes from patients with X-ALD.

**Study design:** Open-label intervention study with biochemical outcome parameters.

**Study population:** Adult patients with confirmed X-ALD (adrenomyeloneuropathy) without contra-indications for the use of bezafibrate are eligible to participate.

**Intervention (if applicable):** Participating patients will receive Bezalip Retard 400 mg for three months, followed by 800 mg during three months.

**Main study parameters/endpoints:** Primary endpoints are cholesterol (total-, LDL-, and HDL-cholesterol) and triglycerides in plasma, VLCFA (C22:0, C24:0 and C26:0) in plasma, leukocytes and erythrocytes, and C26:0-lysophosphatidylcholine in blood. Secondary outcomes are side effects reported by patients and abnormalities in the safety lab.

**Nature and extent of the burden and risks associated with participation, benefit and group relatedness:** The risk of participation is estimated to be low. Bezafibrate is only rarely associated with (reversible) severe adverse reactions (in < 0.01% rhabdomyolysis, thrombocytopenia or leukopenia have been reported).

## 1. INTRODUCTION AND RATIONALE

### *X-linked adrenoleukodystrophy (X-ALD)*

X-linked adrenoleukodystrophy is an inherited metabolic disorder characterised by defective  $\beta$ -oxidation of very long chain fatty acids (fatty acids with a carbon backbone  $\geq 22$ ). The disease is rare: the estimated birth incidence is 1 in 17.000 newborns. The clinical phenotype of the disorder is highly variable. Knowledge of incidence and pathophysiology of X-ALD and peroxisomal disorders in general has increased significantly over the last few decades.

### *Symptoms and disease progression*

The expression and severity of the disease show a large variability, also within the same kindred with identical *ABCD1* mutations and similar environmental influences. This phenotypic variability remains largely unexplained.

Clinically, the disease can be classified into several phenotypes. However, phenotypes can progress to other phenotypes over time. The most frequent phenotype is adrenomyeloneuropathy (AMN). This phenotype becomes manifest in early adulthood (usually in the 3rd decade) and is mainly characterised by myelopathy and peripheral neuropathy with incontinence and spastic paraparesis. The symptoms are gradually progressive and eventually cause significant impairment in the activities of daily living.

X-ALD can also cause severe and rapidly progressive cerebral demyelination in childhood, with the highest incidence between 3 and 10 years of age. This is the Childhood Cerebral ALD (CCALD) phenotype and if not treated by bone marrow transplantation early in the course of the disease is relentlessly progressive and fatal.

### *Pathophysiology*

X-ALD is caused by mutations in the *ABCD1* gene coding for adrenoleukodystrophy protein (ALDP). ALDP is located in the peroxisomal membrane and functions as a transmembrane transport protein involved in transporting VLCFA into the peroxisomal matrix. VLCFA are exclusively degraded by beta-oxidation in the peroxisome. Dysfunction or deficiency of ALDP causes defective beta-oxidation and accumulation of VLCFA. How this VLCFA accumulation causes the symptoms of the disease (e.g. direct toxicity or other indirect mechanisms) remains unclear, but destabilizing effects of VLCFA on the cell membrane has been demonstrated. In the cerebral white matter of patients affected by CCALD there is severe inflammation, but the trigger remains unknown. To date many different *ABCD1* mutations have been described (<http://www.x-ald.nl>), but genotype-phenotype correlation has never been established.

#### *Rationale for the use of bezafibrate in X-ALD*

Recent experiments in cultured fibroblasts from patients with X-ALD show that incubation with bezafibrate can reduce VLCFA levels in these cells by more than 40% with no apparent toxicity ([name] and [name], manuscript in preparation). It is remarkable that this effect does not seem to be caused by increased VLCFA degradation, but rather by inhibiting the synthesis of VLCFA. This is in accordance with previous work on bezafibrate (and several other drugs from the same class), suggesting that this drug can inhibit fatty acid synthesis.

 Follow-up experiments in X-ALD knockout mice showed a reduction of VLCFA accumulation the liver of these animals after 8 weeks of treatment with bezafibrate (administered in the chow). In the plasma of the treated animals we could also detect a decrease in C26:0-lysophosphatidylcholine, a marker for VLCFA accumulation (Hubbard et al., Mol Genet Metab 2006).

These observations provide a rationale for the use of bezafibrate as a possible target compound for the reduction of VLCFA in patients with X-ALD, and therefore a potential new treatment for this disorder that might affect progression of the disease.

Bezafibrate is an approved drug in the Netherlands, and is registered to reduce plasma VLDL- and LDL-lipoprotein concentration (and therefore reduces plasma cholesterol and triglycerides). Currently, it is used for the treatment of hypertriglyceridaemia. This drug has been in use for several decades and is generally considered safe.

The current trial is designed as a “proof of principle” trial. Our aim is to determine if our *in vitro* data and *in vivo* data from mice can be extrapolated to patients with X-ALD. Therefore, we designed a small trial to see if there is indeed a biochemical effect (e.g. reduction of VLCFA). If there is indeed an effect on VLCFA a new large-scale placebo controlled trial with long term follow up and clinical outcome parameters will be necessary.

## **2. OBJECTIVES**

Primary Objective: The primary objective of this study is to determine if bezafibrate can reduce VLCFA in plasma, lymphocytes and erythrocytes and C26:0-lysophosphatidylcholine in patients with X-linked adrenoleukodystrophy.

## **4. STUDY POPULATION**

### **4.1 Population (base)**

The birth incidence of X-linked adrenoleukodystrophy is 1 in 17000 live births (this includes males and female hemizygotes). The AMC is the referral centre for this disorder, and consequently most of the Dutch population visits the AMC for follow-up, about 150 come in for regular check-ups. For this study, we will consider adult male patients with the adrenomyeloneuropathy (AMN) phenotype of X-ALD. There is a patient organisation (Belangenvereniging X-ALD, <http://www.xald.nl>) with a regular newsletter that can help reach patients that do not visit the hospital for follow-up.

### **4.2 Inclusion criteria**

Inclusion criteria for participation in this trial are:

- an age of 18 years or older
- capable of giving informed consent and physically capable of visiting the hospital for follow-up visits
- no contra-indications for the use of bezafibrate, e.g. kidney- and/or liver disease.
- confirmed X-ALD, AMN phenotype (confirmed by VLCFA analysis and mutation analysis of the *ABCD1* gene)

### **4.3 Exclusion criteria**

Exclusion criteria for participation in this trial are:

- use of medication that lowers cholesterol and/or triglycerides (e.g. statins)
- liver disease or and increase in serum CK of more than 3 times the baseline level
- treatment with Lorenzo's oil in the 8 weeks preceding the trial

### **4.4 Sample size calculation**

If 8 patients are enrolled in the trial, a 50% reduction in plasma C26:0 can be detected with a power of 80%, using tandem-MS analysis to determine plasma C26:0 levels.

## **5. TREATMENT OF SUBJECTS**

### **5.1 Investigational product/treatment**

All patients will be treated with bezafibrate (up to 800 mg once daily). Bezafibrate is a drug used for the treatment of hypertriglyceridaemia. For this trial Bezalip Retard tablets will be used, that can be taken once daily. Contra-indications for the use of this medication are liver- and/or kidney disorders. Common side effects include dyspepsia and dizziness. Rare side-effects (< 0.01%) are rhabdomyolysis, thrombocytopenia or leukopenia.

### **5.2 Use of co-intervention (if applicable)**

A co-intervention has not been planned.

### **5.3 Escape medication (if applicable)**

There is no escape medication available. If side-effects are reported or the safety lab done at each visit is abnormal, the medication will be discontinued.

## **6. INVESTIGATIONAL MEDICINAL PRODUCT**

For more detailed information please refer to the SPC for bezafibrate (Bezalip) included with this protocol.

### **6.1 Name and description of investigational medicinal product**

Bezafibrate (Bezalip) Retard 400 mg.

### **6.2 Summary of findings from non-clinical studies**

For more detailed information please refer to the SPC for bezafibrate (Bezalip) included with this protocol, more specifically page 7.

### **6.3 Summary of findings from clinical studies**

Bezafibrate is used to reduce cholesterol and/or triglycerides in patients with hypertriglyceridaemia. There are no trials documenting the effect of bezafibrate on the levels of VLCFA in plasma in patients with X-ALD. The rationale is detailed in the introduction of this protocol.

### **6.4 Summary of known and potential risks and benefits**

Several serious adverse reactions to bezafibrate have been described (rhabdomyolysis, thrombocytopenia and leukopenia) to occur in rare cases (< 0.01%). Pathophysiologically, it is not likely that patients with X-ALD are at greater risk for complications of bezafibrate than the general population. Benefits are unclear. If in this “proof of principle” study we can show that bezafibrate can indeed decrease VLCFA in plasma, leucocytes, and erythrocytes, there will be a rationale for a large clinical trial to determine if there is also clinical benefit for patients with this disorder.

### **6.5 Description and justification of route of administration and dosage**

Bezafibrate can be administered orally. There is a sustained release tablet available (Bezalip Retard) that can be dosed once daily which is more convenient and is probably associated with better compliance than the non-sustained released tablets. In this trial the initial dose is 400 mg Bezalip retard once daily (the standard recommended dose), which will be increased in the second part of the trial to 800 mg once daily to establish if there is a dose-effect relationship.

### **6.6 Dosages, dosage modifications and method of administration**

Bezafibrate will be administered as Bezalip Retard 400 mg once daily for 3 months, then the dosage will be increased to 400 mg twice daily for an additional 3 months. All trial medication will be taken orally.

**6.7 Preparation and labelling of Investigational Medicinal Product**

Medication will be ordered by the hospital pharmacy from Actavis, the manufacturer of Bezalip and labelled according to GCP requirements.

**6.8 Drug accountability**

Drug accountability will be handled by the hospital pharmacy of the AMC. Medication will be ordered through the hospital pharmacy, as well as drug delivery to the researchers for distribution among participating patients.

## **7. METHODS**

### **7.1 Study parameters/endpoints**

#### **7.1.1 Main study parameter/endpoint**

Primary endpoints are cholesterol (total-, LDL-, and HDL-cholesterol) and triglycerides in plasma, VLCFA (C22:0, C24:0 and C26:0) in plasma, leukocytes and erythrocytes, and C26:0-lysophosphatidylcholine in blood.

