#### **7.1.3. Other study parameters (if applicable)**

Other parameters are drop-out and compliance (as measured by an effect on plasma lipids).

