## **9. STATISTICAL ANALYSIS**

### **9.1 Descriptive statistics**

The primary outcome data are continuous variables. Values of these variables will be compared with baseline pre-treatment values, and values obtained during treatment with 400 mg and 800 mg Bezalip. Analysis will be with a two-sided unpaired Student's t-test.

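### Section 7.1.1 ranks 14 endpoints equally as primary, including four plasma lipids outside the primary objective, and names no lead endpoint or success rule

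*Protocol*

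**What the plan says.** Section 7.1.1, repeated in the Summary, sets the primary list: "Primary endpoints are cholesterol (total-, LDL-, and HDL-cholesterol) and triglycerides in plasma, VLCFA (C22:0, C24:0 and C26:0) in plasma, leukocytes and erythrocytes", followed by "and C26:0-lysophosphatidylcholine in blood". All items have the same rank.

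Section 9.1 gives the comparisons: "Values of these variables will be compared with baseline pre-treatment values, and values obtained during treatment with 400 mg and 800 mg Bezalip". It then adds: "Analysis will be with a two-sided unpaired Student's t-test". It states no significance level, no order of testing and no definition of success. Section 6.5 gives the reason for the dose increase, "to establish if there is a dose-effect relationship", which suggests a comparison of 800 mg with 400 mg as well.

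Other sections point to a narrower question:
- Section 2 sets the primary objective: "to determine if bezafibrate can reduce VLCFA in plasma, lymphocytes and erythrocytes and C26:0-lysophosphatidylcholine". Lipids are absent.
- Section 4.4 sizes the trial on one variable: "a 50% reduction in plasma C26:0 can be detected with a power of 80" per cent with 8 patients.
- Section 1 (rationale) makes the large placebo-controlled trial conditional on an effect on VLCFA. Sections 6.4 and 10.4 agree.
- Section 7.1.3 lists among the other parameters "compliance (as measured by an effect on plasma lipids").

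**The concern.** A reader of the results cannot tell from the protocol which of 14 variables, at which dose, answers the primary question. An adjustment method could sit in a separate analysis plan. The choice of primary endpoint belongs in the protocol, and here it disagrees with the protocol's own objective, sample size and criterion for going on.

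Two things are at stake. First, section 1 says the drug is registered to reduce VLDL and LDL, and hence cholesterol and triglycerides. A fall in total cholesterol, LDL-cholesterol or triglycerides would show known pharmacology, yet it would be reported as a primary result. Second, even among the VLCFA and lysophosphatidylcholine measures there are many chances for a spurious reduction, and a reduction is what would lead to the next trial.

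The lipids also have two roles, as primary outcome and as adherence marker. Sections 4.2 and 4.3 do not require raised lipids at entry, so a small lipid change cannot separate a patient who did not take the tablets from one whose lipids did not respond.

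**Working it through.** **Count.** Lipids: total, LDL- and HDL-cholesterol plus triglycerides = 4. VLCFA: 3 acids x 3 matrices = 9. C26:0-lysophosphatidylcholine = 1. Total 4 + 9 + 1 = 14. Two contrasts with baseline give 14 x 2 = 28 tests; adding 800 mg versus 400 mg gives 14 x 3 = 42. Without the lipids, 10 endpoints x 2 doses = 20. (Section 2 says lymphocytes where section 7.1.1 says leukocytes; I treat these as one matrix.)

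**The plan's own figure.** Eight patients, a 50% reduction in plasma C26:0 and 80% power cannot be reproduced, because no SD or alpha is given. At an assumed two-sided 5%, the SD that makes it true is 33.2% of baseline (exact unpaired t, 14 df), 35.7% (unpaired, normal approximation) or, as SD of the change, 43.3% (paired t, 7 df). The claim concerns one variable and one test.

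**Simple bound.** With k independent tests at 5%, the chance of at least one false positive is 1 - 0.95^k: 51.2% for 14, 76.2% for 28 and 88.4% for 42. For reductions only, 1 - 0.975^20 = 39.7%. The tests are not independent, because contrasts share occasions and endpoints are correlated, so I simulated.

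**Simulation.** 40,000 null trials per setting, 8 patients, 3 occasions, two-sided 5% per test (assumed), any one success counting.
- Paired: t = mean change / (SD of change / sqrt 8), 7 df.
- Unpaired, as section 9.1 plans: t = difference in means / sqrt[(s1^2 + s2^2)/8], 14 df.

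Each cell shows endpoint correlation 0, then 0.7.

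| Analysis | Any of 42 | Any of 28 | False reduction, 10 endpoints x 2 doses |
|---|---|---|---|
| Paired | 85%, 57% | 74%, 46% | 38%, 20% |
| Unpaired, within-patient correlation 0 | 84%, 52% | 74%, 43% | 37%, 19% |
| Unpaired, within-patient correlation 0.5 | 33%, 19% | 25%, 14% | 10%, 6% |
| Unpaired, within-patient correlation 0.8 | about 3% | about 2% | about 1% |

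For comparison, a single valid test gives a false reduction 2.5% of the time.

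The unpaired rates are low because the test is wrong for these data. The true variance of a within-patient difference is 2s^2(1 - r), but the unpaired standard error uses 2s^2. The statistic shrinks by about sqrt(1 - r), so the critical value of 2.145 acts like 2.145/sqrt(0.5) = 3.03 at r = 0.5 and 2.145/sqrt(0.2) = 4.80 at r = 0.8.

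**Lipids.** No lipid effect size or SD is given. For assumed standardised effects of 0.5, 1.0 and 1.5, one unpaired test with 8 values per occasion has power 15%, 46% and 80%. At least one of three independent lipids is then significant with probability 39%, 84% and 99%. A significant lipid result is therefore possible, and how likely it is depends on figures the protocol does not contain.

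**Alternatives.** Bonferroni over 14, 28 or 42 tests uses 0.00357, 0.00179 or 0.00119, and cuts the stated 80% power for C26:0 to 36%, 27% or 22% (exact unpaired t, at the SD of 33.2%). Dropping only the lipids still leaves 20 or 30 tests (30 = 10 x 3). One named endpoint and contrast leaves one test and keeps the stated sizing.

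**The case against.** This is a small proof-of-principle pilot, and several points in its favour stand.

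- A reader might infer that a positive primary result is to be expected whatever happens to VLCFA. The protocol does not support that. It defines no positive primary result, gives no lipid effect or SD, has 8 patients, and ties the follow-up trial to VLCFA in three places. A lipid fall alone would not trigger that trial under the text.
- A reader might infer that all four lipids are registered targets. Section 1 supports three; it does not name HDL-cholesterol.
- A reader might take 85% or 38% as the error rates of the plan as written. They are the rates for a paired analysis. Section 9.1 plans an unpaired one, whose rates are lower, and the 42 count needs a third contrast that section 9.1 leaves open.
- The 5% level is assumed. If every endpoint had to succeed, there would be no inflation. The text does not say which rule applies.
- No rule excludes non-compliant patients, so it would be speculation to say that a null VLCFA result would be explained away as poor adherence.

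What these points leave untouched is the conflict within the protocol: lipids are primary in one section, outside the objective in another and a compliance marker in a third, and no lead endpoint is named although the sizing uses one. Nor does the low unpaired error rate reassure, since it comes from a mismatched test and disappears once the pairing is respected.

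**Conclusion.** The point holds. Fourteen endpoints are ranked equally as primary over two or three contrasts, with no lead endpoint or success rule, and this contradicts the primary objective, the sample size basis and the stated condition for the next trial. A significant primary result is possible without any VLCFA effect, through three registered lipid effects or through chance.

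The size depends on three assumptions: any one success counts, each test is at two-sided 5%, and endpoint correlation lies between 0 and 0.7. A paired analysis then gives 20% to 38% for a false VLCFA or lysophosphatidylcholine reduction over two doses, and 57% to 85% for any of 42 tests. As written, unpaired, the figures are about 6% to 10% and 19% to 33% at within-patient correlation 0.5, and about 1% and 3% at 0.8. The inflation appears in full once the test is corrected to a paired one, so the two matters should be settled together.

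**What to change.** In section 7.1.1 and the Summary, name plasma C26:0, the variable the trial is sized on, as the single primary endpoint. State one contrast with baseline and the alpha, and test the other dose against baseline next in fixed sequence. The protocol does not settle which dose leads; section 4.4 names none, so the sponsor must choose and state it before data are seen.

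Keep the remaining VLCFA measures and C26:0-lysophosphatidylcholine as key secondary endpoints under the same objective. Move cholesterol and triglycerides out of the primary list to section 7.1.3 as pharmacodynamic and compliance parameters.

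The cost is rewording of sections 7.1.1 to 7.1.3, the Summary and section 9.1, with no extra patients or samples. The downside is small: the other measures become supportive. Returned-tablet counts would give an adherence measure independent of lipid response, but they are an optional new procedure, since section 6.8 covers ordering and delivery and does not provide for them.
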